## **9.9 Cohort Size and Rules for Cohort Advancement**

### **9.9.1 Arms and DLT observation periods**

Subjects will be enrolled onto one of three Arms, as described in Section 5.1.1 Treatment Arm assignment. The first 3 subjects treated will be enrolled only on Arm A or B and will be  $\geq 15$  years and  $\leq 26$  years at time of enrollment. Subjects may be enrolled on Arm C once 3 subjects have been treated on Arm A and/or Arm B, and at least 1 subject on Arm A or B completes Course 2 without experiencing a DLT. Within each Arm subjects will be assigned to successive DRs in Cohorts of up to 3 subjects. Dose escalation rules will be applied separately for each Arm. There will be a  $\geq 7$ -day interval before enrollment of the initial subject onto the other

Arm. [For example, if the initial subject on Arm B is enrolled on 7 July 2018, the initial subject for Arm A cannot be enrolled until  $\geq$  14 July 2018.]

A modified 3+3 statistical design will be used for determining DR assignment with specific details below for determination of a Maximally Tolerated Dose Regimen (MTDR), followed by an expansion cohort. Within each Arm, treatment will begin with DR 1, Course 1. After the first subject completes Course 1 (i.e., completes the seven-day observation period following the last CAR T cell infusion of Course 1) the subsequent 2 subjects may be treated. Subjects within DR1 of each arm may only receive their initial CAR T cell infusion after the previously treated subject completes Course 1. Subjects enrolled in subsequent cohorts may only receive their initial CAR T cell infusion no sooner than 14 days following the date the previously treated subject received their initial CAR T cell infusion. Before the cohorts for the next (higher) DR may open, all 3 subjects of the prior (lower) DR must have received at least 1 of the maximally intended doses in Course 2 and completed a 7-day observation period following the final infusion occurring in Course 2 and not have experienced dose closure as noted below.

If the current Cohort is fully accrued, receiving therapy, but is not yet completely evaluated for DR DLTs, or if the cumulative number of DLTs at the current DR (including subjects still undergoing evaluation) exceeds 2, then a new subject cannot be assigned to the current DR. Instead, the subject may be offered (a) treatment at the DR below the DR currently being evaluated or (b) to wait until that current Cohort has been completely evaluated to receive treatment in the next DR as per study design. A subject treated under this provision may serve as a member of the current or the next cohort of three at that DR if the trial resumes regular accrual at that same DR or if the trial resumes at the next higher DR but subsequently de-escalates to revisit that DR.

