**Figure 5-7 Arm C Dose Regimen 4**

[figure not shown]

Subjects enrolled in Arm C DR 4 will receive Course 1 consisting of DL 1 on Week 1 and DL 3 on Week 3 followed by a rest during Week 4, with clinical evaluations.

Course 2 will commence for subjects meeting criteria for subsequent CAR T cell infusion (Section 5.5.2). Subjects will receive DL 4 on Weeks 1 and 3, followed by a rest during Week 4 with disease evaluation, including radiographic restaging.

Following Course 2, subjects meeting criteria for further CAR T cell infusion (Section 5.5.2) may receive additional Courses of therapy until subject meets criteria for removal from protocol therapy, intolerable toxicity, or depletion of available manufactured CAR T cells. The DLs for Courses 3 and beyond will be no higher than DL 4 or the dose at which no DLTs were experienced by the subject during Courses 1 and 2. A lower DL may be administered based on availability of CAR T cells, see Section 5.1.2 Dose Regimen assignment.

Treatment will be administered on Weeks 1 and 3 followed by a rest week every fourth week. Disease restaging evaluations will occur as indicated in the schedule of procedures.

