## 5.2 Dose-Limiting Toxicity (DLT)

A DLT is an event, defined below, which, in the opinion of the investigator, is possibly, probably, or definitely attributable to the CAR T cell product and which occurs from the time of initial CAR T cell infusion through 28 days following the final CAR T cell infusion. The Maximum Tolerated Dose Regimen (MTDR) will be established by the occurrence of DLTs which occur from the time of initial CAR T cell infusion through 7 days following the final CAR T cell infusion received during Course 2. See Section 9.9.4 Definition and determination of MTDR and RP2DR, for information on establishing MTDR.

The definition of a DLT includes all  $\geq$  Grade 3 Common Terminology for AEs (CTCAE) v5 toxicities **except**  $\geq$  Grade 3 toxicities that are known to be related to CAR T cells [45], listed below.

Exceptions to  $\geq$  Grade 3 DLTs:

- Grade 3 CRS that decreases to  $\leq$  Grade 2 within 72 hours of onset
- $\geq$  Grade 3 hypotension, fever, chills not controlled with medical intervention that decrease to  $\leq$  Grade 2 within 72 hours
- $\geq$  Grade 3 activated PTT, fibrinogen, and/or INR that are asymptomatic and resolve within 72 hours
- $\geq$  Grade 3 hypoglycemia and/or electrolyte imbalance that are asymptomatic and resolve within 72 hours
- $\geq$  Grade 3 nausea and/or vomiting that decrease to  $\leq$  Grade 2 within 7 days

- Arm A and B only: Grade 3 neurological adverse event that decreases to  $\leq$  Grade 2 within 7 days
- Arm C only: Grade 3 neurological adverse event that decreases to  $\leq$  Grade 2 within 21 days (treatment with dexamethasone and/or bevacizumab is allowed)

The definition of a DLT also includes any related toxicity lasting  $> 14$  days which prohibits the subject from meeting criteria for subsequent CAR T cell infusion.

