#### **9.5 Safety and Tolerability**

Subjects receiving any CAR T cell product will be eligible for safety and tolerability analyses. If a subject is removed from study prior to receiving the initial CAR T cell infusion, they will be replaced. For the purpose of assessing overall safety and tolerability, subjects will be evaluated for toxicities for up to 28 days following final CAR T cell infusion. For the purposes of escalation of DR and defining Maximal Tolerated Dose Regimen (MTDR), subjects in the existing cohort will be evaluated for toxicities from the time of initial CAR T cell infusion through 7 days following the final CAR T cell infusion received during Course 2, or until they commence with alternate therapies for their CNS tumor, whichever comes first. Subjects who are taken off study prior to Day 28 of Course 2 and have experienced a DLT will count towards that DR's evaluable accrual and will not be replaced. For all Arms, if a subject is removed from study prior to Day 28 of Course 2 for reasons other than toxicity (e.g., progressive disease requiring immediate alternative therapy) and has not received at least one dose of the maximally intended dose level per the assigned DR, they will be replaced before cohort advancement is permitted. Subjects who die before Day 28 of Course 2, and before receiving alternative therapy, and whose death is due to CAR T cell related toxicity will meet the definition of DLT and will not be replaced. Subjects who die before Day 28 of Course 2 due to reasons other than CAR T cell related toxicity and have not experienced a DLT will be replaced before cohort advancement is permitted.

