### **9.9.2 Dose Regimen (DR) escalation rules**

A subject will be considered DR escalation-evaluable if they are evaluable for MTDR DLT and are counted as part of a 3-subject dose escalation Cohort according to the rules described below.

The following rules will be applied separately and independently for each Arm. DLTs are defined in Section 5.2.

*Dose escalation rules using a modified 3 + 3 design for Arms A, B, and C.* DRs are detailed in Section 5.1.3.

1. Escalation and de-escalation decisions will use cohorts of 3 consecutive toxicity-evaluable subjects treated at the same DR
2. The dose escalation route will be similar to a 3+3 design, and will allow expansion on the tentative MTDR if 1 DLTs out of the first cohort of 3 and 1 DLTs out of the second cohort of 3 were observed
  - a. If 0 DLTs out of the first cohort of 3 (0/3) within a DR, and there is a DR available for escalation, it will escalate to the next DR. If there is no DR

available for escalation, then this DR is considered as tentative MTDR and another cohort of 3 will be treated at the current DR.

- b. If 1 DLTs out of the first cohort of 3 (1/3), a second cohort of 3 will be treated and evaluated at the current DR
  - i. If 0 DLTs out of the second 3 and there is a DR available for escalation, it will escalate to the next DR. If there is no DR available for escalation (1 DLT in first 6), the MTDR will be estimated
  - ii. If 1 DLTs out of the second cohort of 3 (i.e. 2 DLT in the first 6), a third cohort of 3 will be treated at the current DR. If there are 0 DLTs in the third cohort of 3, the MTDR will be estimated. If there is 1 DLT in the third cohort (i.e. 3 DLTs in the first 9), a final cohort of 3 will be treated at the current DR and the MTDR will be estimated once all subjects have been evaluated.
- c. If 2 or more DLTs out of any cohort of 3 ( $\geq 2/3$ ) toxicity-evaluable subjects, the current DR will be shut down and the DR will de-escalate to the previous DR. If the first 2 subjects of any cohort of 3 both experience DLTs and the third subject has not received CAR T cells, stop the cohort at 2 subjects and de-escalate to previous DR and the third subject will become the first subject of a new cohort. If there is no DR available for de-escalation (lowest), the arm will be shut down.

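### The next Dose Regimen may open 7 days after the last Course 2 infusion, but an Arm C Grade 3 neurologic event can take up to 21 days to be settled as DLT or exempt, and no rule covers an event still open at that point

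*Protocol*

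**What the plan says.** **The gate.** Section 9.9.1 requires all three subjects of the lower DR to have received at least one of the maximally intended Course 2 doses and to have "completed a 7-day observation period following the final infusion occurring in Course 2 and not have experienced dose closure as noted below". Section 9.5 uses the same cut-off for escalation and for the maximum tolerated dose regimen (MTDR): toxicities are assessed "through 7 days following the final CAR T cell infusion received during Course 2". Section 5.2 repeats it for the MTDR.

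**The classification rule.** Section 5.2 counts every related Grade 3 or higher toxicity as a DLT, apart from listed exceptions. One begins "Arm C only: Grade 3 neurological adverse event that decreases to" Grade 2 or below, and allows 21 days for this. The Arm A and B counterpart allows 7 days. A separate sentence adds as a DLT any related toxicity that lasts more than 14 "days which prohibits the subject from meeting criteria for subsequent CAR T cell infusion".

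**The decision.** Section 9.9.2 acts on small counts. The rule that begins "If 0 DLTs out of the first cohort of 3 (0/3) within a DR" escalates if a higher DR is available; 1/3 adds a second cohort of three at the same DR; two or more in any cohort of three shuts the DR.

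**Accrual while a cohort is under evaluation.** Section 9.9.1 also bars new assignments to a DR whose full cohort is not yet completely evaluated. It offers a new subject the DR below, or a wait for the next DR until evaluation is complete. It does not define complete evaluation, and the only period it states is the 7-day one.

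**The concern.** The gate is a fixed number of days after an infusion. The classification of some events depends on how long they last. Where the permitted resolution time is longer than the wait, an event can begin inside the observation window and still be neither a confirmed DLT nor a confirmed exception when the next DR may open. The gap is widest in Arm C, where the resolution time is three times the wait.

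Events near the end of Course 2 also carry the most information for the decision. In Arm C DR 2 to DR 4 the top dose level is given only in Course 2; for DR 4, for example, "Subjects will receive DL 4 on Weeks 1 and 3". With cohorts of three, the handling of one open event fixes the next step. Section 5.2 adds a second uncertainty: it refers to DLTs that occur by the cut-off, without saying whether an event is dated by its onset or by the day on which it fails the duration test.

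**Working it through.** The protocol gives no figure for this point, so there is nothing to reproduce. The check is a timeline, followed by an illustration.

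**Inputs.** Arm C Course 2 infusions in Weeks 1 and 3 (Section 5.1.5), nominally Day 1 and Day 15. Observation of 7 days after the final Course 2 infusion (Sections 5.2, 9.5, 9.9.1). Resolution time of 21 days in Arm C and 7 days in Arms A and B (Section 5.2).

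**Gate:** 15 + 7 = Day 22.

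**Latest classification day** = onset day + resolution time. **Gap** = latest classification day − 22.

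| Onset (Course 2 day) | Arm C settled by | Gap after gate | Arms A/B settled by | Gap after gate |
|---|---|---|---|---|
| 1 | 22 | 0 | 8 | none |
| 2 | 23 | 1 | 9 | none |
| 8 | 29 | 7 | 15 | none |
| 15 (final infusion) | 36 | 14 | 22 | 0 |
| 22 (end of window) | 43 | 21 | 29 | 7 |

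In Arm C, any in-window event starting on Day 2 or later can therefore be open at the gate. If it starts on or after the final infusion, the gap is 14 to 21 days. In Arms A and B only events starting after the final infusion are affected, for at most 7 days. These are ceilings: an event that resolves sooner is settled sooner, and the Arm C neurologic exception covers Grade 3 only. Where the 14-day clause applies, onset on Days 15 to 22 is decided no earlier than Days 29 to 36, which is also after the gate.

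**Which subject.** After DR 1, initial infusions are at least 14 days apart (Section 9.9.1). When the third subject reaches the gate on schedule, the first is at least 28 days past their own gate, beyond the 21-day maximum, and the second at least 14 days past. The open event will mostly be in the last-treated subject, but one is enough.

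**Illustration of the decision.** Under Section 9.9.2 a DR escalates after 0/3, or after 1/3 followed by 0/3. With DLT probability p and q = 1 − p:

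P(escalate) = q³ + 3pq² × q³

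At p = 0.34, the limit in Section 9.9.4: 0.2875 + 0.4443 × 0.2875 = 0.415. Suppose that a share f of true DLTs is undecided at the gate and counted as none, so that p becomes p(1 − f). The protocol gives no value for f, so a range is shown.

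| True DLT rate | f = 0 | f = 25% | f = 50% |
|---|---|---|---|
| 34% | 0.415 | 0.589 | 0.773 |
| 50% | 0.172 | 0.351 | 0.600 |

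This shows the direction and possible size of the effect under that handling. It does not predict what this trial will see.

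**The case against.** **An open event may be a DLT by default.** Section 5.2 includes all related Grade 3 or higher events except those that do decrease in time, so an unresolved event has not yet earned its exception. This is a fair reading, and under it the illustration above does not apply. But the protocol does not state it, and does not say what happens to the count if the event later resolves in time.

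**The 7 days may be a minimum.** The wording on complete evaluation can be taken to cover open events, the weekly review in Section 9.11.1 looks at adverse events and DLTs, and Section 9.9.3 lets the Study Chair shut a DR at any time. But complete evaluation is undefined, and the other two safeguards do not say how an open event is to be counted.

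**The next cohort does not go straight to a higher level.** This stands. Every DR starts at DL 1, and Course 1 never exceeds the lower DR's maximum. In Arm C, Course 1 tops out at DL 1, DL 2 and DL 3 in DR 2, DR 3 and DR 4, which are the maxima of DR 1, DR 2 and DR 3. A higher level comes in the new cohort's Course 2, nominally its Day 29, 28 days after a start at the gate and so later than the 21-day maximum gap. A reader might infer that subjects receive an untested level while an event is open; on the nominal schedule they do not. What remains is assignment to the wrong DR and, in DR 3 and DR 4, receipt of the lower DR's top level in Week 3 of Course 1, 14 days after such a start, when an event that began after the lower cohort's final infusion could still be open.

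**Stronger readings that the text does not support.**
- A reader might infer that withholding the Week 3 infusion moves the gate to Day 8. Week 3 is not due until Day 15, and Section 5.1.6 allows a delay of up to 3 weeks, to Day 36, so nobody can know on Day 8 that Week 1 was the final infusion.
- A reader might infer that the 14-day and 21-day clauses contradict each other. The 14-day sentence is worded as an addition to the definition, so it reads as a further route to a DLT. It needs a clarification only.
- A reader might infer that the MTDR rate is permanently biased downward. If DLTs are dated by onset, a late-classified event still enters the cumulative Course 1 and 2 rate in Section 9.9.4.

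**Conclusion.** The concern holds as a mismatch between a fixed-day gate and duration-based DLT classification, with no rule for events open at the gate. On the nominal schedule the unclassified period lasts up to 21 days past the gate in Arm C (14 to 21 days for onset on or after the final infusion) and up to 7 days in Arms A and B. It arises only for an event that starts in the window and does not resolve early.

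The consequence lies in the decision rule. One event separates 0/3 (escalate) from 1/3 (second cohort), or 1/3 from 2/3 (shut the DR). A cohort can thus be assigned to a higher DR when the lower one should have been expanded or closed, or more subjects can be added to a DR that should have been shut. The delay before higher dose levels are reached limits the harm but does not correct the assignment. How often this would happen cannot be derived from the protocol.

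**What to change.** Reconcile Sections 5.2, 9.5 and 9.9.1:

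1. Open the next DR only when the DLT status of every event with onset inside the observation window has been determined, and define complete evaluation of a cohort in Section 9.9.1 in those terms.
2. State that DLTs are attributed to the escalation and MTDR window by date of onset, so that an event settled later still counts.
3. As a clarification, say in Section 5.2 whether the 14-day clause applies to an Arm C neurologic event that meets the 21-day exception.

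The clinical durations are for the sponsor to settle; this point takes no view on them.

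The cost is amendment wording and, only when such an event is open at the gate, a wait of up to about 3 weeks in Arm C (Day 43 instead of Day 22 at most). For the neurologic clause in Arms A and B the wait is at most 7 days. A cohort with no open event proceeds as now.

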#### **9.9.4 Definition and determination of MTDR and RP2DR**

The MTDR is defined as the highest DR with at least six DLT-evaluable subjects, whose cumulative DLT rate during Courses 1 and 2 is below 34%. The MTDR will be estimated separately for each Arm.

Per investigator discretion and with DSMB approval, if a DR lower than the selected MTDR displays satisfactory disease response and has at least six DLT-evaluable subjects, then this DR can be chosen as the RP2DR instead of the MTDR.

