#### **9.10 Expansion Cohort**

Following determination of the safety and toxicity of each arm based on our modified 3+3 design, an expansion cohort of up to 12 subjects in each arm will be started with treatment at the MTDR/RP2DR. The purpose of the expansion cohort is to provide a more precise assessment of the tolerability and toxicity of this treatment when dose at the MTDR/RP2DR as well as gain additional knowledge regarding secondary and exploratory objectives with particular focus on the duration and magnitude of in vivo persistence of CAR T cells in the cerebral spinal fluid including descriptions of cellular and protein components.

The expansion cohort will begin once the MTDR/RP2DR has been determined. For the expansion cohort, up to 12 additional subjects will be treated. Accrual to the expansion cohort will be continuous and will not depend upon the completion of treatment of the previous patients in the expansion cohort. Ongoing safety monitoring will occur during the expansion cohort with analysis in combination with all subjects treated at the MTDR/RP2DR. If at any time the DLT rate appears to exceed 33%, infusions would be halted to allow review with the Data Safety Monitoring Board (DSMB). Examples include a DLT rate of 3/7-9, 4/10-12, 5/13-15, 6/16-18, or 7/19-21.

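### At 3 DLTs in 9 and 4 in 12 the rules in 9.9.1, 9.9.2, 9.9.4 and 9.10 conflict, and 9.9.4 does not say whether a shut Dose Regimen can be the MTDR

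*Protocol*

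**What the plan says.** Four parts of Protocol section 9 act on the DLT count at a DR.

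- **9.9.1 (accrual bar).** When the cumulative DLT count at the current DR "exceeds 2, then a new subject cannot be assigned to the current DR". The cap is a bare count with no denominator. It is a separate condition, joined by 'or' to the one about a cohort still under evaluation.
- **9.9.2 (escalation).** After 0/3 at the highest DR, "this DR is considered as tentative MTDR and another cohort of 3 will be treated at the current DR" (rule 2a). After 1/3 and 1/3, "i.e. 2 DLT in the first 6), a third cohort of 3 will be treated at the current DR"; after a further 1/3, "i.e. 3 DLTs in the first 9), a final cohort of 3 will be treated at the current DR", and the MTDR is then estimated (rule 2b.ii). "If 2 or more DLTs out of any cohort of 3", then "the current DR will be shut down and the DR will de-escalate to the previous DR" (rule 2c). After de-escalation, a DR with fewer than six evaluable subjects is filled up and the MTDR re-estimated (rule 2d).
- **9.9.4 (MTDR definition).** The highest DR with at least six DLT-evaluable subjects "whose cumulative DLT rate during Courses 1 and 2 is below 34" percent.
- **9.10 (expansion).** Safety is judged on expansion subjects together with everyone already treated at the MTDR/RP2DR. Infusions are halted for DSMB review if the rate appears to exceed 33%: "Examples include a DLT rate of 3/7-9, 4/10-12, 5/13-15", continuing to 7/19-21.

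No passage ranks these rules.

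**The concern.** Defining the MTD and RP2DR is a primary objective (sections 2.1 and 9.2), and these counts decide it. If two sections give different orders on the same data, two things depend on which section the study team opens: whether three more children are treated at a DR, and whether that DR is declared the MTDR. The rule that governs should be fixed before the data are seen.

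**Working it through.** **Inputs.** From the protocol: the 9.9.1 cap (more than 2 DLTs), the 9.9.2 cohort rules, the 9.9.4 limit (below 34%, n at least 6), and the 9.10 limit (above 33%) with its list. The true DLT rate p is my assumption, because the protocol gives none. I use 20%, 25% and one third.

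**Step 1: reproduce the 9.10 list.** For n = 7 to 21, take the smallest r with r/n > 0.33. This gives 3 for n = 7-9, 4 for 10-12, 5 for 13-15, 6 for 16-18 and 7 for 19-21, exactly the printed list. Requiring r/n > 1/3, or r/n at least 0.34, would instead need 4/9, 5/12, 6/15, 7/18 and 8/21. So the printed list counts a rate of exactly one third as a halt.

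**Step 2: apply every rule to the counts in question.** 2/6 = 3/9 = 4/12 = 33.33%, which is above 33% and below 34%.

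| Cohorts | Count | 9.9.1 | 9.9.2 | 9.9.4 limit | 9.10 list |
|---|---|---|---|---|---|
| 1+1 | 2/6 | open | third cohort | met | not listed |
| 0+2 | 2/6 | open | shut, de-escalate | met | not listed |
| 1+1+1 | 3/9 | barred | final cohort here | met | listed, but expansion not begun |
| 1+1+1+0 | 3/12 | barred | estimate MTDR | met (25%) | no halt |
| 1+1+1+1 | 4/12 | barred | estimate MTDR | met (33.3%) | halt |

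- *3/9:* 9.9.2 orders three more subjects at the DR; 9.9.1 forbids assigning any.
- *4/12:* a DR on the 1+1+1+1 path has never been escalated past, so it is the highest one tried. It meets 9.9.4 and opens expansion. Because 9.10 pools those 12 subjects, the halt is met before the first expansion subject.
- *3/12 and 4/12:* the 9.9.1 bar, read as written, also conflicts with expansion at that DR.
- *0/3 then 2/3:* reachable at the top DR (rule 2a) or when a de-escalated DR is filled to six (rule 2d). Rule 2c shuts the DR, but six subjects at 33.3% satisfy 9.9.4, which does not exclude a shut DR.

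**Step 3: how often.** Let a_k = C(3,k) p^k (1-p)^(3-k).

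| Quantity | p = 0.20 | p = 0.25 | p = 1/3 |
|---|---|---|---|
| a0 | 0.512 | 0.422 | 0.296 |
| a1 | 0.384 | 0.422 | 0.444 |
| a2 | 0.096 | 0.141 | 0.222 |
| 3/9 = a1^3 | 5.7% | 7.5% | 8.8% |
| 4/12 = a1^4 (subset of 3/9) | 2.2% | 3.2% | 3.9% |
| 0/3 then 2/3 = a0 × a2 | 4.9% | 5.9% | 6.6% |

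The first two probability rows apply to any DR on first pass. The last applies only at an arm's top DR, because lower DRs escalate after 0/3. For a de-escalated DR already at 0/3, the chance of 2/3 in the filling cohort is a2: 9.6%, 14.1% and 22.2%.

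**The case against.** The strongest case on the other side limits the scope.

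- **Not every one-third count conflicts.** A reader might infer that 2/6 always gives opposite orders. By 1/3 + 1/3 it does not: two DLTs do not exceed 2, rule 2b.ii orders a third cohort, the 9.9.4 limit is met, and expansion has not begun.
- **The 9.10 halt is a pause.** It allows DSMB review and closes nothing, and it applies only once an MTDR/RP2DR is set. A reader might infer that 4/12 both clears and closes the DR; the text supports only clearing it and halting it at once. This leaves the 3/9 conflict untouched, since 9.10 plays no part in it, and pooling still makes the halt at 4/12 immediate.
- **Rule 2d does not revive a shut top DR.** After de-escalation the current DR is the lower one, so re-estimation is directed there. What remains is the silence of 9.9.4 on shut DRs. The tension between 2c and 2d arises only while a de-escalated DR is being filled to six.
- **Frequency.** Adding the 3/9 and 0/3-then-2/3 terms gives about 11-15%. A reader might apply that sum to every DR, but it holds only at an arm's top DR, where both paths are open. At a true rate of 10% it falls to 1.4% + 2.0% = 3.4%.

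Weekly safety review and the DSMB (section 9.11) could settle a case when it arises, but neither section says which rule prevails.

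**Conclusion.** The point holds in three parts of unequal weight. The 3/9 conflict between 9.9.1 and 9.9.2 is direct: one orders treatment that the other forbids, and the same bar stands against expansion after 3/12 or 4/12. At 4/12, the 34% and 33% limits fall on either side of one third, so a DR can be declared the MTDR with its expansion halt already met. The 0/3-then-2/3 case is narrower: an MTDR definition that does not exclude a DR just shut.

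Per DR on first pass, 3/9 has a probability of 5.7% to 8.8% over assumed true DLT rates of 20% to one third, and 4/12, within it, 2.2% to 3.9%. The third case has 4.9% to 6.6%, at an arm's top DR only. These figures assume independent subjects and a constant rate within the DR. The textual conflicts do not depend on them. Because they affect a primary objective, they should be corrected.

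**What to change.** Reconcile 9.9.1, 9.9.2(b)-(d), 9.9.4 and 9.10 so that each reachable count has one stated action. A single decision table would do this, covering 0/3, 1/3, the 2/2 early stop, 2/3 or more, 0/6, 1/6, 2/6 by path, 3/6 and above, 2/9, 3/9, 4/9 and above, 3/12, 4/12, and 5/12 and above. In particular:

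- make the 9.9.1 cap and rule 2b.ii consistent, and say whether the cap applies to expansion;
- state in 9.9.4 whether a DR shut under rule 2c can be the MTDR;
- reconcile the 34% limit with the 9.10 halt list so that a DR cannot enter expansion with its halt already met. The two limits need not be the same number.

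Which action or limit governs at each count is for the sponsor and DSMB. The cost is amendment wording and one table, with no extra patients.
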